## Background

Colorectal cancer (CRC) is the second most common cause of all cancer deaths in Europe and the Western world with a lifetime risk of approximately 5% [1]. Despite the implementation of early detection programs about 20–25% of all patients have already synchronous metastases at the time of diagnosis and approximately 25–50% will develop metastases in the course of disease mainly in liver and lung [2, 3]. Liver metastases are the main cause of death and the only currently available curative therapy is the surgical R0 resection of metastases. Without any further treatment the median survival after metastases detection is poor with about 7.5 month [4].

For patients with unresectable disease several systemic treatment options are available. In recent years prognosis has been improved with median survival rates in clinical trials of up to 30 months [5]. The optimal treatment strategy is highly depending on the aim of the treatment, e.g. prolongation of survival, downsizing with secondary (potentially curative) resection, improving tumor-related symptoms, stopping tumor progression and/or maintaining quality of life, the side effect profile of the regimen, tumor -specific factors and comorbidities of the patient.

Combination chemotherapy regimens with 5-fluorouracil/leucovorin/oxaliplatin (FOLFOX) or 5-fluorouracil/leucovorin/irinotecan (FOLFIRI) provide higher response rates, longer progression-free survival (PFS) and better overall survival (OS) in first-line treatment compared to monotherapy regimens with 5-fluorouracil/leucovorin alone.

For patients with a good performance status and adequate organ function second-line chemotherapy should be offered. The chemotherapy regime in this situation is highly depending on the previous therapies, the therapy-free interval and pre-existing toxicities.

For patients who received an irinotecan-based regimen as first-line treatment the second-line treatment should consist of an oxaliplatin-containing combination (FOLFOX or capecitabine/oxaliplatin). For patients who received an oxaliplatin-based regimen as first-line treatment, the second-line treatment should be irinotecan-based (FOLFIRI or irinotecan alone) [6, 7].

The combination of conventional chemotherapy with molecular targeted therapies such as the anti-vascular endothelial growth factor (anti-VEGF) agents bevacizumab, ramucirumab and aflibercept or the anti-epidermal growth factor receptor (anti-EGFR) agents cetuximab and panitumumab should be considered depending on the tumor biology. After second-line chemotherapy many patients are still in a good condition to receive third-line treatment depending on the organ function and pre-existing toxicities.

Despite the recent improvements in CRC therapy there is still the need of developing new treatment strategies for patients with metastatic chemorefractory disease. One important pathway which is constitutively active in 90% of CRC is the canonical Wnt/β-catenin pathway [8].

The S100 calcium binding protein A4 (S100A4) was identified as a Wnt/β-catenin target gene [9]. S100A4, originally named metastasin 1 (MTS1), is associated with many physiological processes (e.g. migration, invasion, wound healing, neovascularisation). S100A4 is able to induce metastases in different experimental in vitro and animal models [10–13]. S100A4 is overexpressed in many different types of cancer [14, 15]. Its overexpression correlates with poor patients’ prognosis; high S100A4 levels are prognostic for metachronous metastases formation and correlate with reduced patient survival in several cancer types [16–22]. However, S100A4 itself is not tumorigenic as shown by Ambartsumian et al. because transgenic mice with an overexpression of S100A4 do not develop tumors per se [23].

In our own group we identified niclosamide as a transcriptional inhibitor of S100A4 expression by performing a high throughput screen for the human S100A4 promoter–driven reporter gene expression. Niclosamide is used since mid of the 1960s as an anti-helminthic drug which inhibits glucose uptake, oxidative phosphorylation and anaerobic metabolism [24]. Niclosamide is approved by the Food and Drug Administration (FDA) and the European medicines agency (EMA) for treatment of tapeworm infections.

Consequently, we demonstrated the efficacy of niclosamide in cell culture by inhibition of S100A4-induced cell migration and invasion. We identified niclosamide as anti-metastatic drug in colon cancer xenografted mice by restriction of liver metastases linked to shorter survival. In this experimental setting, niclosamide interfered in the Wnt signaling pathway by disrupting the complexation of β-catenin/TCF with the S100A4 promoter leading to reduced expression of S100A4 [13].

Other studies reported that niclosamide also interfered with the Wnt signaling pathways by inhibiting Wnt/Frizzled 1 signaling or by inducing the degradation of the Wnt co-receptor low density lipoprotein receptor-related protein 6 (LRP6) [25, 26]. Osada et al. demonstrated a niclosamide-induced decrease in Dvl2 expression, leading to reduced downstream β-catenin signaling [27]. In hepatocellular cancer cells, niclosamide reduced cell proliferation, induced apoptosis, decreased TOP activity, and lowered β-catenin, Dvl2 and cyclin D1 levels [28]. Ono et al. reported niclosamide-induced reduction of proliferation of primary human leiomyoma cells by inhibiting Wnt/β-catenin pathway activation, such as inhibited TOP activity, down-regulated pathway target genes e.g. Axin2, and reduced nuclear β-catenin translocation [29]. Londoño-Joshi et al. demonstrated niclosamide-reduced levels of LRP6 and β-catenin for basal-like breast cancers [30]. For ovarian cancer, niclosamide treatment resulted in increased cytotoxicity, reduction of Wnt/β-catenin signaling by TOP assay, and decreased Wnt pathway proteins e.g. Axin2 and cyclin D1 [31]. King et al. demonstrated niclosamide-induced abrogation of Wnt7A/β-catenin signaling, inhibition of β-catenin transcriptional activity, cell viability, and decrease in cell migration [32]. Satoh et al. showed that niclosamide inhibited cell proliferation, induced caspase-dependent apoptosis and G1 cell cycle arrest, and decreased cell migration, reduced the level of mediators of epithelial-to-mesenchymal transition, and decreased β-catenin expression, [33]. Functionally, niclosamide is able to block further pathways besides Wnt/β-catenin signaling, known to be decisive for cancer initiation, progression and metastases [34, 35]. For instance, it inhibits the mTORC1 activity by lysosomal dysfunction in different cancer types [36–38], blocks the STAT3 phosphorylation and its translocation to the nucleus in prostate cancer cells [39], and inhibits the NF-κB and Notch pathways [40, 41]. Thus, niclosamide has been reported as an anti-cancer molecule in numerous cancer types like CRC [13], osteosarcoma [42], breast cancer [30, 37], ovarian cancer [31, 43], prostate cancer [44], non-small cell lung cancer (NSCLC) [45, 46], glioblastoma [40], head and neck cancer [47], multiple myeloma, and leukemia [41, 48].

Niclosamide has only little side effects and seems to be well tolerated even when applied over a long period [49]. The oral dose of niclosamide for adults in anti-helminthic treatments is 2 g on day one followed by 1 g daily for 6 consecutive days. The serum concentration of niclosamide after a single dose of 2 g leads to maximal serum concentrations of 0.25–6.0 μg/ml which corresponds to the concentration used on the above mentioned models [34, 49].

As there is strong evidence from in vitro and in vivo experiments that niclosamide might be beneficial as anti-tumorigenic and anti-metastatic drug we designed the hereafter described clinical trial to investigate the safety and efficacy of orally applied niclosamide in patients with metachronous or sychronous metastases of a CRC who progressed after therapy and for whom no other standard therapy is available.

## Methods/Design

### Study aims

This study evaluates the safety and efficacy of orally applied niclosamide in patients with metachronous or synchronous metastases of CRC origin, who progressed under previous therapy.

### Study objectives

Primary objective is PFS after 4 months. PFS after 4 months will be evaluated according to the Response Evaluation Criteria In Solid Tumors (RECIST) Version 1.1.

Secondary objectives are OS, time to progression, disease control rate (remission + partial remission + stable disease), and safety.

Pharmacokinetic analysis will be done to investigate niclosamide plasma concentration and a potential correlation with efficacy.

### Study design

The study is a phase II single center, one-arm open-label clinical trial for patients with metastatic CRC.

### Study schedule

The trial has started on August 2015. The estimated accrual duration is 30 months. The estimated study completion date is 2018 (final data collection, date for primary outcome measure). Survival status will be collected for 2 years after registration.

### Trial organization

The trial is organised by the Charité Comprehensive Cancer Center (CCCC) in collaboration with the Max-Delbrück-Center for Molecular Medicine (MDC), Berlin, Germany.

### Statistics

The study is a one-arm open-label clinical trial with interim analyses for futility of patients with metastatic CRC.

A Simon two-stage design will be used to allow early termination due to futility. The null hypothesis is that the probability of being free of progression (having stable disease, partial or complete response) at 4 months is p_0_ = 0.25 (H_0_: p < =p_0_ = 0.25) estimated according to the recent literature [50, 51]. This null hypothesis will be tested with the Binomial test one-sided against the alternative H_1_ (estimated progression-free probability at 4 months of the experimental therapy) p1 = 0.5. Samples size for both stages were calculated according to the optimal design after Simon [52].

In the first stage 17 patients will be recruited. If less than 5 of the first 17 patients are progression-free at 4 months the trial will be terminated prematurely. Otherwise 20 additional patients will be enrolled (up to a total of 37 patients).

The null hypothesis will be rejected if at least 13 patients out of 37 will be free of progression at 4 months. This design (optimal design after Simon) yields a type I error rate of 0.046 and a power of 0.902.

Analyses of PFS and OS survival will performed with Kaplan-Meier-curves, hazard ration will be reported with 95% confidence intervals. For safety analysis the worst toxicities in each cycle will be reported according to the National Cancer Institute (NCI) Common Terminology Criteria for Adverse Events (CTCAE) Version 4.03. A descriptive analysis of adverse events (AEs) and serious adverse events (SAEs) will be provided.

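### The printed boundary of 13/37 does not hold the stated type I error of 0.046 under any binomial calculation, and the named Binomial test is not tied to the two-stage design

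*Protocol article*

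**What the plan says.** Everything relevant is in the Statistics section of the protocol article.

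- Design: "A Simon two-stage design will be used to allow early termination due to futility". The sample sizes are attributed to Simon's optimal design.
- Hypotheses: the null progression-free probability is given as "at 4 months is p_0_ = 0.25 (H_0_: p < =p_0_ = 0.25" and the alternative as "estimated progression-free probability at 4 months of the experimental therapy) p1 = 0.5".
- Test: "This null hypothesis will be tested with the Binomial test one-sided". The section does not say whether the test is computed on 37 patients as a single sample or over the two stages.
- Stage 1: "In the first stage 17 patients will be recruited", and "If less than 5 of the first 17 patients are progression-free at 4 months the trial will be terminated prematurely".
- Stage 2: "Otherwise 20 additional patients will be enrolled (up to a total of 37 patients".
- Final rule: "The null hypothesis will be rejected if at least 13 patients out of 37 will be free of progression at 4 months".

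For this design the section reports a type I error of 0.046 and power of 0.902. It prints no separate nominal significance level.

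**The concern.** The named test, the rejection boundary and the stated error rates should describe one decision procedure, and they do not. A count of 13/37 is declared a success, yet it is unremarkable under a null rate of 0.25 by any binomial calculation, with or without allowance for the futility stop.

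This is the only confirmatory decision in a single-arm trial of at most 37 patients. If the rule is applied as printed, an inactive treatment has about a one in ten chance of being declared active, against a stated risk of under one in twenty. If the cut-offs are corrected but the test sentence is left alone, someone could still set an ordinary binomial p-value beside the boundary and find that the two disagree at the boundary itself.

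**Working it through.** **Inputs (Statistics section):** p0 = 0.25, p1 = 0.50, n1 = 17, n2 = 20, N = 37; stop if at most 4 of 17; reject if at least 13 of 37. The 0.05 level used below is an assumption. The conclusions are the same with the stated 0.046.

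**Formula.** Let X1 ~ Bin(17, p) and X2 ~ Bin(20, p) be independent. If the trial stops at X1 ≤ a and rejects at X1 + X2 ≥ r, then

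P(reject | p) = Σ over x from a+1 to 17 of C(17, x) p^x (1−p)^(17−x) × P(X2 ≥ r − x).

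**Step 1: can the stated 0.046/0.902 be reproduced from the printed rule?** Put a = 4 and r = 13:

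- p = 0.25: Σ over x = 5..17 of C(17, x) 0.25^x 0.75^(17−x) × P(Bin(20, 0.25) ≥ 13 − x) = **0.0988**
- p = 0.50: the same sum with 0.50 = **0.9594**

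They cannot. The type I error is 0.0988/0.046 ≈ 2.1 times the stated value.

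**Step 2: which cut-offs reproduce the stated figures?**

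| Stop if at most | Reject if at least | Type I error | Power |
|---|---|---|---|
| 4/17 (printed) | 13/37 (printed) | 0.0988 | 0.9594 |
| 4/17 | 14/37 | 0.0537 | 0.9375 |
| 4/17 | 15/37 | 0.0261 | 0.8972 |
| 5/17 | 13/37 | 0.0793 | 0.9184 |
| **5/17** | **14/37** | **0.0459** | **0.9021** |
| 5/17 | 15/37 | 0.0235 | 0.8694 |

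Only 5/17 with 14/37 gives 0.046 and 0.902; moving one cut-off alone is not enough. A search over all two-stage designs up to N = 42, with type I error at most 0.05 and power at least 0.90 (both assumed targets), returns this same design as Simon's optimal one. Its expected sample size under the null is 17 + (1 − 0.7653) × 20 = 21.7. The printed stop gives 17 + (1 − 0.5739) × 20 = 25.5.

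**Step 3: the named test read as a plain, fixed-sample binomial test.** P(Bin(37, 0.25) ≥ k):

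| k | One-sided p |
|---|---|
| 13 | 0.1109 |
| 14 | 0.0577 |
| 15 | 0.0272 |

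Read this way, the test needs 15/37 at either 0.05 or 0.046.

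**Step 4: what remains after the cut-offs are corrected.** The two-stage rule and the plain test then disagree only at exactly 14/37 (0.0459 against 0.0577). If the plain test governed, the boundary would be 15/37, with type I error 0.0235 and power 0.8694, a loss of 0.9021 − 0.8694 = 0.033. That loss is also the probability of landing on exactly 14/37 when p = 0.50. Under the null the probability is 0.0459 − 0.0235 = 0.022. At intermediate true rates it is larger: 0.093 at 0.35 and 0.099 at 0.375.

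**The case against.** The best defence starts from where the test sentence stands. It follows the announcement of the Simon design and directly precedes the statement on stage-wise sample sizes. Simon's error rates are themselves exact binomial probabilities, so naming a one-sided Binomial test may only identify the kind of calculation used inside that design. A reader might infer that the plan treats the 37 patients as a fixed sample and ignores the futility stop. The text does not say so, and that inference is not made here.

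The defence can add that the rejection rule is explicit and no p-value threshold is printed. A reader might infer that the primary conclusion is undetermined at 13 or 14 of 37. That needs two things the article does not state: a fixed-sample calculation and a 0.05 level. The objection stands to that extent. It is also right that the mismatch at 13/37 comes mainly from the cut-offs, not from the choice of test. Removing the test sentence alone would leave a rule with type I error 0.099.

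A reader might also want to fault the article for not specifying a bias-adjusted estimate or a design-based confidence interval for the 4-month rate. An article may leave those to the full protocol or analysis plan, and it does not say that an unadjusted proportion will be reported.

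The charitable reading does not rescue the printed boundary. With the two stages fully allowed for and the printed futility stop kept, 13/37 corresponds to 0.0988 and 14/37 to 0.0537, both above 0.046.

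**Conclusion.** The point holds in two parts of unequal weight.

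1. The decision threshold is wrong as written. The printed rule carries a type I error of 0.099 and power of 0.959, not 0.046 and 0.902. Both cut-offs are one too low for the stated figures. A likely explanation, though only an inference, is that 5/17 and 13/37 were the largest counts leading to stopping and to non-rejection, and were put into words as less than 5 and at least 13. This part needs only the article's own inputs.
2. The named test is not tied to the two-stage boundary. With the cut-offs corrected this matters only at exactly 14/37, where the two-stage value is 0.0459 and the plain binomial p-value 0.0577. The effect, if the plain test were allowed to govern, is power of 0.869 instead of 0.902. This part is conditional on a fixed-sample reading and on a significance level of 0.05 (or 0.046), neither of which the article fixes as a p-value criterion.

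The text should be corrected before the primary analysis. The documents do not show that the plan intends an analysis that disregards the two stages.

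**What to change.** - Reconcile both cut-offs with the stated 0.046/0.902: rejection at 14 or more of 37, with the matching stage 1 rule of stopping at 5 or fewer of 17. If the printed cut-offs are what was intended, the stated error rates must be replaced by 0.099 and 0.959 and the design no longer described as the optimal one for the stated figures.
- State that the two-stage boundary alone decides the primary conclusion.
- State that any accompanying p-value is computed from the two-stage sampling distribution (0.0459 at 14/37), not from a binomial test on 37 patients as a single sample.

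This takes a few sentences. Sample size, assessments and data collection are unchanged. Only the stage 1 continuation rule and the final threshold each move by one patient.

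### The printed cut-offs (stop below 5 of 17, reject at 13 or more of 37) are each one patient too low: the true type I error is 0.099, not the stated 0.046

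*Protocol article*

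**What the plan says.** Everything needed for an exact check is in the Statistics section of the protocol article.

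- Null: the progression-free probability "at 4 months is p_0_ = 0.25 (H_0_: p < =p_0_ = 0.25".
- Alternative: "estimated progression-free probability at 4 months of the experimental therapy) p1 = 0.5".
- Test: "This null hypothesis will be tested with the Binomial test one-sided against the alternative".
- Design: "Samples size for both stages were calculated according to the optimal design after Simon".
- Stage 1: "In the first stage 17 patients will be recruited", with the futility rule "If less than 5 of the first 17 patients are progression-free at 4 months the trial will be terminated prematurely". Otherwise 20 more patients are enrolled, for a total of 37.
- Final decision: "The null hypothesis will be rejected if at least 13 patients out of 37 will be free of progression at 4 months".
- Claimed properties: the design "yields a type I error rate of 0.046 and a power of 0.902".

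No other section of the article restates or changes these cut-offs.

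**The concern.** By convention, the constants of a Simon design, r1/n1 and r/n, are the largest counts that still lead to stopping or to not rejecting. A design listed as 5/17 and 13/37 therefore stops at 5 or fewer and rejects only above 13, that is, at 14 or more. The article uses the same two numbers the other way round: 5 is the smallest count that continues and 13 the smallest that rejects. Both boundaries would then sit one patient on the lenient side, while the error rates beside them belong to the stricter design.

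This is the rule that decides whether niclosamide is declared active on the primary endpoint, in a one-arm trial with no concurrent control to temper a false positive. A final count of exactly 13, or an interim count of exactly 5, would be decided the opposite way from the design whose error rates are quoted.

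**Working it through.** **Inputs (all from Statistics):** p0 = 0.25, p1 = 0.50, n1 = 17, n2 = 20, n = 37, one-sided.

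**Formula.** Let a be the smallest stage 1 count that continues and c the smallest total that rejects. Then

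P(reject | p) = Σ from x = a to 17 of P(X1 = x) · P(X2 ≥ c − x), with X1 ~ Bin(17, p) and X2 ~ Bin(20, p).

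The type I error is this sum at p = 0.25, and the power is the sum at p = 0.50.

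**Step 1: which rules give the stated 0.046 and 0.902?** Take a = 6, c = 14. At p = 0.25:

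| x | P(X1 = x) | P(X2 ≥ 14 − x) | product |
|---|---|---|---|
| 6 | 0.12761 | 0.10181 | 0.01299 |
| 7 | 0.06684 | 0.21422 | 0.01432 |
| 8 | 0.02785 | 0.38283 | 0.01066 |
| 9 | 0.00928 | 0.58516 | 0.00543 |
| 10 | 0.00248 | 0.77484 | 0.00192 |
| 11 or more | | | 0.00058 |

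The sum is 0.0459. The same sum at p = 0.50 is 0.9021. These are the article's figures. Over all pairs (a, c) for 17 + 20 patients, no other pair rounds to either 0.046 or 0.902.

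**Step 2: the rules as printed.** Take a = 5, c = 13. At p = 0.25:

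| x | P(X1 = x) | P(X2 ≥ 13 − x) | product |
|---|---|---|---|
| 5 | 0.19142 | 0.10181 | 0.01949 |
| 6 | 0.12761 | 0.21422 | 0.02734 |
| 7 | 0.06684 | 0.38283 | 0.02559 |
| 8 | 0.02785 | 0.58516 | 0.01630 |
| 9 | 0.00928 | 0.77484 | 0.00719 |
| 10 | 0.00248 | 0.90874 | 0.00225 |
| 11 or more | | | 0.00061 |

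The sum is 0.0988. At p = 0.50 it is 0.9594. The ratio to the stated type I error is 0.0988 / 0.046 ≈ 2.1.

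**Step 3: how much each boundary contributes.**

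| Continue at | Reject at | Type I error | Power |
|---|---|---|---|
| ≥ 5 of 17 (printed) | ≥ 13 of 37 (printed) | 0.0988 | 0.9594 |
| ≥ 6 of 17 | ≥ 13 of 37 | 0.0793 | 0.9184 |
| ≥ 5 of 17 | ≥ 14 of 37 | 0.0537 | 0.9375 |
| ≥ 6 of 17 | ≥ 14 of 37 | 0.0459 | 0.9021 |

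The final boundary does most of the damage, but correcting it alone leaves the error above 0.05.

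**Step 4: is the stricter version the named design?** The article gives only achieved values, so targets of type I error ≤ 0.05 and power ≥ 0.90 are assumed here. An exhaustive search for the smallest expected sample size under p0 returns n1 = 17, n = 37, stop at 5 or fewer, reject at 14 or more. This is 5/17, 13/37 in Simon's notation.

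**Step 5: effect on the interim look.** At p = 0.25:

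- Stop at 4 or fewer (printed): probability of stopping 0.574; expected sample size 17 + 20 × (1 − 0.5739) = 25.5.
- Stop at 5 or fewer: probability 0.765; expected sample size 17 + 20 × (1 − 0.7653) = 21.7.

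**The case against.** The article may simply contain a slip that the full protocol or the SAP does not share, in which case the conduct of the trial would be unaffected. That may be so, but the cut-offs are plain running prose, not a damaged table, and the published statement would still contradict itself.

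A second objection concerns a tempting supporting argument. At 13 of 37 (35.1%) the exact one-sided 95% lower limit is 22.2%, below the null of 25%. That figure is correct, but it does not separate the wrong boundary from the right one: at 14 of 37 the limit is 24.5%, also below 25%, and the fixed-sample one-sided p-value is 0.058. The fixed-sample limit ignores the futility stop, which removes some paths to rejection and brings the error down to 0.046. This objection stands, so the case should rest on the two-stage error rates alone. Those do separate the boundaries: with the stricter interim rule, the error is 0.079 at a cut-off of 13 and 0.046 at 14.

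Third, 0.099 is not the effect of the final boundary alone, and the 0.05 and 0.90 targets are not printed. Both points are correct. They affect how the finding is described, not whether it holds.

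**Conclusion.** The concern holds. The printed decision rules and the printed error rates belong to different designs. As written, the type I error is 0.099 instead of 0.046, and the power 0.959 instead of 0.902. The first figure reflects both misplaced boundaries. The printed futility rule is also weaker than that of the optimal design the article names: under the null it stops early 57% of the time instead of 77%, at an average cost of about 3.8 more patients (25.5 − 21.7).

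These results use only the article's own inputs and exact binomial probabilities. The single added assumption, targets of 0.05 and 0.90, is needed to identify the design as Simon's optimal one, not to show the contradiction. This must be fixed because it concerns the trial's main go/no-go decision.

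**What to change.** First check which boundaries the full protocol and SAP contain. Then make the rules and the error rates agree in one of two ways:

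1. Keep 17 and 37 patients, 0.046 and 0.902, and change both cut-offs: stop if 5 or fewer of the first 17 are progression-free at 4 months, and reject the null hypothesis if 14 or more of 37 are (that is, more than 13).
2. If the printed rules are to stand, state a type I error of 0.099 and power of 0.959, and drop the description as the optimal design.

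The first option restores the design whose properties are quoted. Either option changes two figures (plus the design label in the second) and adds no patients. If the slip is only in the article, an erratum is enough. If the full protocol has the same text, an amendment is needed. Because the trial is open-label and began in August 2015, the amendment should record whether any 4-month outcomes were known when the boundaries were corrected.
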